**Methods/design:**

The study is a randomized controlled trial comparing a single verum acupuncture treatment with two active comparators: sham acupuncture and dietary recommendations. Sample size calculation revealed a total of 75 patients pending an alpha of 0.05, a power of 0.8, and an estimated effect size of 0.80. Patients with breast cancer undergoing platinum- or taxane-based chemotherapy will be included if they present with phantogeusia (abnormal taste sensations without an external oral stimulus) with an intensity of 4 points or above on an 11-point numeric rating scale (NRS). The primary outcome is phantogeusia; secondary outcomes include parageusia (abnormal taste of food), hypogeusia (reduced taste sensations), hypergeusia (increased taste sensations), xerostomia (dry mouth), stomatitis, appetite, and functional impairment. All outcomes will be assessed at baseline and prior to the next chemotherapy administration using an 11-point NRS for each. All adverse events will be recorded.

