### Randomization

A researcher who was not involved in conducting the study generated a stratified (by age and type of chemotherapy because both variables are found to affect the course of dysgeusia [23, 24]) random allocation sequence with randomly varying block lengths using Random Allocation Software [25]. The randomization list is password-secured, and no person other than the aforementioned researcher is able to access it. On the basis of this list, the researcher prepared sealed and opaque envelopes sorted in ascending order of randomization. Allocation to the groups will be executed by the study physician, who is involved in neither the random sequence generation nor the assessment of study outcomes.

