### Data collection

Baseline data will be assessed before randomization (T_0_) and will include social demographics (age, sex, family status, education, employment), medical data of the patient (tumor type, staging, grading, relapse, menopausal status, chemotherapy type), and ratings for baseline outcome data.

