### Secondary outcomes

Secondary outcomes include phantogeusia, assessed between T_1_ and T_2_ using a daily patient log, as well as parageusia (abnormal taste of food), hypogeusia (reduced taste sensations), hypergeusia (increased taste sensations), xerostomia (dry mouth), stomatitis symptoms, appetite, and functional/social impairment, assessed at T_2_ and between T_1_ and T_2_ using a daily patient log with 11-point NRSs, respectively.

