### Statistical analysis

Data will be analyzed using IBM SPSS Statistics for Windows software, release 22.0 (IBM Corp., Armonk, NY, USA). Patients’ characteristics will be presented separately for each group using descriptive statistics, including mean and standard deviation, median and range, frequencies and proportions, based on the data format and distribution.

Data analysis will be conducted according to the intention-to-treat principle; that is, all randomized patients regardless of compliance or withdrawal will be included. Missing values will be multiply imputed by the Markov chain Monte Carlo method [37, 38], yielding a total of 50 complete datasets. Statistical tests will be conducted in a hierarchical order, starting with the comparison of acupuncture vs. usual care, which in case of significant effects will be followed by the comparison of acupuncture vs. sham acupuncture.

The primary outcome will be analyzed as a function of the treatment group (verum acupuncture versus standard medical care), patients’ expectations, and their respective baseline values (linear covariates) using a univariate analysis of covariance. Between-group differences and 95% confidence intervals were estimated using two-sided *t* tests and an alpha level of 5%. If the analysis reveals a statistically significant between-group difference, a second univariate analysis of covariance on the primary outcome will be conducted as a function of the treatment group (verum acupuncture versus sham acupuncture), patients’ expectations, and their respective baseline values (linear covariates). Between-group differences and 95% confidence intervals were estimated using two-sided *t* tests and an alpha level of again 5%. Because of hierarchical testing of the hypotheses, no alpha level adjustment is necessary [39]. The same covariance models will be applied for secondary outcome measures; for those effect measures, confidence intervals and *P* values will be reported descriptively. Moreover, a Kaplan-Meier survival analysis will be used to analyze group differences regarding the time point of symptom relief based on the daily patient log. Data on tolerability and safety will be reported descriptively. No interim analysis will be conducted.

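### Time to symptom relief is compared by Kaplan-Meier without covariates, although the collected baseline rating and expectancy enter the plan's ANCOVAs; if baseline intensity predicts relief, this supplementary comparison loses power

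*Protocol article*

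**What the plan says.** All references are to the Protocol article.

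- **Statistical analysis, time to relief:** "a Kaplan-Meier survival analysis will be used to analyze group differences regarding the time point of symptom relief based on the daily patient log". No covariate, stratum, regression model or test is named.
- **Statistical analysis, primary outcome:** the model contains treatment group, patients' expectations "and their respective baseline values (linear covariates) using a univariate analysis of covariance".
- **Statistical analysis, secondary outcomes:** "The same covariance models will be applied for secondary outcome measures; for those effect measures, confidence intervals and" P values are to be reported descriptively.
- **Secondary outcomes:** "Secondary outcomes include phantogeusia, assessed between T_1_ and T_2_ using a daily patient log". The same log is the source for time to relief.
- **Data collection:** the assessment at T0, before randomization, includes "ratings for baseline outcome data".
- **Participants:** entry requires an average phantogeusia score of at least 4 on an 11-point scale, so scores of 4 to 10 if the scale is scored 0 to 10.
- **Randomization:** the sequence is "stratified (by age and type of chemotherapy because both variables are found to affect the course of dysgeusia". Baseline intensity is not a stratification factor.

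**The concern.** The authors treat expectations and the starting value as worth adjusting for wherever they fit a covariance model, yet the method named for time to relief uses neither. The entry range is wide. If relief means falling to a fixed score, a patient who starts at 9 has further to go than one who starts at 4, and starting intensity could then explain much of the variation in time to relief.

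Two things follow if baseline is prognostic. The unadjusted comparison has less power than the collected data allow. And because the design does not balance baseline intensity, a chance difference between arms of 25 carries into the relief curves of this one trial. Recruitment was still under way when the article appeared (Trial status), so the method could still be settled before analysis.

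**Working it through.** **1. The plan's own figure.** Sample size calculation gives 25 per group for d = 0.8, two-sided alpha 0.05 and power 0.8. The normal formula gives n = 2(1.960 + 0.842)²/0.8² = 24.5, so 25 per arm (power 0.807). The exact t test gives 0.791 at n = 25 and needs 26. The figure reproduces within one patient. It concerns the primary comparison only; no figure is given for time to relief.

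**2. Chance imbalance in baseline.** The standard error of the difference in means is SD × √(2/25) = SD × 0.283. The SDs are assumptions.

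| Assumed baseline, scores 4 to 10 | SD | SE | P(difference ≥ 0.5) | P(difference ≥ 1) |
|---|---|---|---|---|
| Uniform | 2.0 | 0.57 | 38% | 7.7% |
| Skewed to low scores | 1.67 | 0.47 | 29% | 3.4% |

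**3. Power with and without baseline, by correlation.** The model is 25 against 25, log time to relief with correlation rho to baseline, a group shift of 0.8 SD and about 88% to 90% of patients relieved. All of these are assumptions except the arm size and the 0.8, which is borrowed from the sample size section.

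| Error distribution of log time | rho | Unadjusted | Adjusted | Gain (points) |
|---|---|---|---|---|
| Normal | 0 | 72% | 72% | 0 |
| Normal | 0.3 | 71% | 75% | 4 |
| Normal | 0.5 | 69% | 81% | 12 |
| Extreme-value | 0 | 93% | 93% | 0 |
| Extreme-value | 0.5 | 78% | 96% | 18 |

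A separate run with a 21-day log gave 94% against 92% at rho 0, 88% against 93% at 0.3, 84% against 94% at 0.4 and 80% against 96% at 0.5: gains of −2, 5, 10 and 16 points.

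**4. The same question by hazard ratio.** Assumptions: baseline uniform on 4 to 10, median relief 14 days in controls who start at 7, censoring at 21 days, treatment hazard ratio 2.25, about 36 to 39 events, 2,000 runs per setting. An unadjusted log-rank test is set against a baseline-adjusted Cox model.

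| Hazard ratio for relief per baseline point | Log-rank | Adjusted Cox | Gain (points) |
|---|---|---|---|
| 1.00 | 0.71 | 0.66 | −5 |
| 0.85 | 0.64 | 0.65 | about 0 |
| 0.75 | 0.54 | 0.64 | 10 |
| 0.65 | 0.42 | 0.61 | 19 |

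The 5-point loss in the first row is best read as an upper end. The two tests there also differ in how they handle tied days (the Cox fit used the Breslow method). When the same Cox model was fitted with and without baseline (step 3), the loss at rho 0 was 0 to 2 points.

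**5. Type I error.** With no treatment effect, the unadjusted log-rank test rejected in 4.2% to 6.3% of runs. The Cox fits with and without baseline in the 21-day run rejected in 3.8% to 7.3% (800 runs per setting). Both are near the nominal 5%.

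**The case against.** The case for leaving the plan alone is substantial.

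- **The analysis is an addition.** It stands outside the two-step confirmatory sequence and has no power target. Daily-log phantogeusia is itself a secondary outcome to which the adjusted models apply. This stands, and limits the point to an improvement.
- **The mechanism depends on what relief means.** The article names neither the symptom nor a threshold for it. A relative-change definition would weaken the link with baseline. This stands, and is why the loss is stated conditionally.
- **Adjustment can cost power.** At no association it costs about 0 to 5 points. This stands.
- **The test, strata or a supporting model may be set out in the full protocol or analysis plan.** This is fair for the name of the test. But the article does fix a method, and that method takes no covariates; the point is about that choice, not about a missing detail.

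A reader might also infer more than the documents support:

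- **That baseline phantogeusia enters every other efficacy model.** It does not: each ANCOVA uses the baseline of its own outcome.
- **That the power loss is certain.** No baseline-to-relief association is given, and weak associations cost nothing.
- **That chance imbalance biases the test.** It shifts the estimate in a given trial, but the test keeps its level over repeated randomization.
- **That disagreement with the ANCOVA could come only from the missing adjustment.** The primary ANCOVA concerns the rating at T2, while this analysis concerns when relief occurs between T1 and T2. These quantities can differ legitimately.

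**Conclusion.** The point holds as a minor, conditional improvement. The unadjusted comparison is valid but leaves out a baseline rating and an expectancy measure that the trial already collects and uses in its ANCOVAs. Under assumed associations the power given up runs from about 0 points (no or weak association) to roughly 4 to 18 points at correlations of 0.3 to 0.5; the hazard-ratio version gives up to 19 points at 0.65 per baseline point. These figures rest on assumed baseline distributions, relief rates, effect sizes and, in the runs that state a horizon, a 21-day log; the article does not restrict cycle length. Expectancy was not simulated, so its inclusion rests on consistency with the ANCOVAs, not on a computed gain. The primary conclusion is unaffected.

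**What to change.** Keep the Kaplan-Meier curves for display. Base the group comparison on a Cox model for time to relief with treatment group, the T0 rating of the symptom analysed and expectancy. Fit it for verum versus standard medical care and for verum versus sham, and report each hazard ratio with its 95% confidence interval descriptively, like the other secondary results. The symptom and the definition of relief must be settled, here or in the full plan, before the model can be fitted.

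The cost is one sentence of analysis wording, with no new data, visits or patients. There are three downsides: proportional hazards must be checked; the hazard ratio is conditional on the covariates and so is not the quantity that the marginal curves show; and about 0 to 5 power points may be lost if baseline turns out not to be prognostic. With the 36 to 39 events assumed in step 4 of the working, three covariates leave at least 36/3 = 12 events each.

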## Discussion

Dysgeusia is often discussed as a less impairing, less significant side effect of chemotherapy. For patients, however, taste distortions during chemotherapy greatly affect appetite and quality of life, with few available effective treatment options [3, 6, 10]. Acupuncture as a relatively simple and short intervention that did not show severe side effects during the application of chemotherapy [17] and preliminary effects in patients with idiopathic dysgeusia [13] appears to be an important subject of research. The present trial was rigorously designed according to the CONSORT and STRICTA recommendations, including a nonpenetrating sham needling control, blinding of outcome assessors and patients, controlling of blinding success and expectation effects, and the use of standardized NRSs [22]. Particularly regarding the design of an ideal sham acupuncture control procedure, researchers broadly discussed how to mimic best the procedure of acupuncture and control for unspecific effects of expectation, conditioning, and therapeutic attention without provoking specific physiological effects [40–42]. It was argued that noninvasive sham acupuncture appears to be a more suitable control condition than the minimally invasive approach. In this study, using a noninvasive sham procedure should be feasible and blindable because participants do not have a visual control.

This trial should therefore generate the first evidence for the efficacy and effectiveness of hypoglossal acupuncture in patients with breast cancer who have acute chemotherapy-induced dysgeusia. Results can provide suitable information for further sham protocols and clinical acupuncture trials.

## Trial status

This randomized clinical trial is currently recruiting participants.

## Data Availability

Not applicable.

## Abbreviations

CONSORT: Consolidated Standards of Reporting Trials
NRS: Numeric rating scale
SPIRIT: Standard Protocol Items: Recommendations for Interventional Trials
STRICTA: Standards for Reporting Interventions in Clinical Trials of Acupuncture
T: Time point
TNM: Tumor, node, metastasis, classification of malignant tumors
